### Main trial secondary objectives

Clinical effectiveness:To compare other metrics of sore throat severity including responses on the Tonsillectomy Outcome Inventory 14 (TOI 14) [25] and STARs for any sore throat episodes experiencedTo compare Quality of Life (QOL) as measured by the Short Form 12 Health Survey (SF-12) [26] longitudinally during study follow-upTo report the number of adverse events, visits to the GP/walk-in clinic/Accident and Emergency (A&E), prescriptions issued and additional interventions required for sore throats and related events through STAR data, and supported by data linkage to primary care participant recordsTo adjust the estimate of effectiveness in light of other baseline covariates including severity of tonsillitisTo evaluate the impact of alternative sore throat patient pathways by observation and statistical modelling of outcomesTo assess to what extent trial participants are representative of the total population of sore throat patients referred to ENT clinicsEconomic evaluation:To compare Quality-Adjusted Life Years (QALYs) using the Area Under the Curve (AUC) method based upon SF-6D scores derived from the SF-12 [26] responses [27] measured at baseline, throughout the study and during any episodes of sore throat experiencedTo compare the cost-effectiveness measured in terms of the incremental cost per sore throat day avoided from the perspective of the NHS and patients over 24 monthsTo compare the cost-utility based on incremental cost per QALY gained from the perspective of the NHS and participants over 24 monthsTo compare the cost-benefits based on the perspective of the NHS and participant’s willingness to pay to avoid a sore throat day using the NATTINA contingent valuation questionnaire ‘Value of Avoiding a Sore Throat Day’ administered at baseline and information on the number of sore throat days experienced.Qualitative process evaluation: to document the views, experiences and acceptability of patients and clinicians regarding tonsillectomy and conservative management, and how patient experience may shape future researchFuture research: to propose further research questions based on the findings of the trial analyses

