### Data collection and follow-up

All participants will be followed up for 24 months from the date of randomisation. Once consented, the participant will complete a baseline questionnaire booklet to be returned to NCTU. The participating site will then randomise the participant via the NCTU randomisation system. Participants randomised to immediate tonsillectomy will undergo surgery within 6–8 weeks of randomisation. All NATTINA participants will be prompted weekly by their preferred method of communication (short message service (SMS) message, Email or Interactive Voice Response (IVR) via telephone) to submit the number of sore throat days experienced in the previous 7 days, and requested to submit a STAR when they experience a sore throat. Through this the participant will provide details of the severity, use of any over-the-counter and prescription medications, the nature of any professional health care advice sought and the number of hours when unable to undertake usual activities (including work/studies). An additional SF-12 [26] will also be completed relative to the episode. The research nurse will contact participants randomised to the surgical arm at 1 and 2 weeks after their tonsillectomy to collect data concerning any adverse events. The participant will be asked to attend 2 further clinic visits and complete follow-up questionnaire booklets at 12 and 24 months, and to complete 2 other questionnaire booklets at home at 6-month and 18-month interim points. The 12-month clinic visit will allow participants in the conservative management group to be assessed on their willingness to remain in the deferred group. At their final 24-month visit these participants will be asked whether they wish to go forward for tonsillectomy. Adverse events and SAEs related to the study intervention will be collected throughout the duration of the study.

Consent will be sought to access participants’ GP health records in order to gather primary health care usage data at the end of their 24-month follow-up. Data collected will cover the participant’s 24-month follow-up and 12 months prior to randomisation, and will capture adverse events, number of contacts with primary and secondary health care services, prescribing information and other relevant material to support data retrieved from STARs and post-operative research nurse telephone calls (Table 1).

**Table 1 Tab1:** Data collection and time points

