Measure	Baseline	Weekly (baseline to 24-month FU)	Sore throat episode	Surgery	6-month FU	12- month FU	18- month FU	24- month FU
'About You' Questionnaire	X							
'Value of Avoiding a Sore Throat Day' Questionnaire	X							
TOI 14	X				X	X	X	X
SF-12	X		X		X	X	X	X
Health Service Utilisation Questionnaire	X				X	X	X	X
Participant Time and Travel Questionnaire							X	
Comparison data (declining patients)	X							
Weekly alert		X						
Sore Throat Alert Returns (STAR)			X					
CRF	X			X	X	X	X	X
GP Linkage Data								X

*CRF* Case Report Form, *FU* follow-up, *SF-12* Short Form 12 Health Survey, *TOI 14* Tonsillectomy Outcome Inventory 14

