### Statistical analysis

The primary outcome measure of the total number of sore throat days reported over the 24 months of follow-up will be analysed using negative binomial regression in order to compare any change between the NATTINA arms while adjusting for the stratification variables used – recruiting centre (as a random effect) and baseline severity (as a fixed effect). This analysis will be undertaken on an intention-to-treat basis; however, participants may switch over from conservative to surgical management. In the NATTINA design, although participants are asked to commit to ‘deferred surgery’, we anticipate that a number of participants will take up the opportunity to switch to surgery. The implication of such cross over, which typifies surgical trials, is that the intention-to-treat analysis will produce a very conservative estimate of the effect of tonsillectomy. We will, therefore, undertake a planned ‘as treated’ analysis with repeated measures corresponding to two periods of follow-up for those participants who cross over from medical management to tonsillectomy. The length of these follow-up periods will act as an exposure variable in the negative binomial regression.

QOL scores based on the SF-12 will be calculated according to the scoring manual at baseline and 6, 12, 18 and 24 months post randomisation. The scores will be analysed using models developed for longitudinal data. The dependent variable will be the QOL score for an individual patient at a particular occasion. Both variation between patients and variation between occasions nested within patients will be modelled as random effects with a normal distribution. Differences between groups and changes over time will be modelled as fixed effects. The analysis will be adjusted for the differences between strata.

The analysis of other secondary outcomes will follow a broadly similar strategy; repeated measures will be analysed using a random effects model with an appropriate error structure. Should data be found to be non-normally distributed, the use of transformations or non-parametric approaches will be considered.

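### STAR severity and impact exist only for episodes that occur, so comparing arms on them under the article's random effects rule would not give a randomised treatment effect

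*Protocol article*

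**What the plan says.** All references are to the protocol article.

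- **Data collection and follow-up.** Every participant is prompted weekly for the number of sore throat days, and is "requested to submit a STAR when they experience a sore throat". On content: "Through this the participant will provide details of the severity, use of any over-the-counter and prescription medications", as well as advice sought and hours lost from normal activity. In addition, "An additional SF-12 [26] will also be completed relative to the episode". Table 1 ties the STAR to the sore throat episode and not to the scheduled follow-up points.
- **Main trial secondary objectives.** One objective is "To compare other metrics of sore throat severity including responses on the Tonsillectomy Outcome Inventory 14 (TOI 14) [25] and STARs", restricted to episodes that participants go on to have. The list of secondary outcome measures repeats this for STAR frequency, severity and impact.
- **Statistical analysis.** The SF-12 model comes first: "The dependent variable will be the QOL score for an individual patient at a particular occasion". The other secondary outcomes are to follow a broadly similar strategy, in which "repeated measures will be analysed using a random effects model with an appropriate error structure".
- **Missing data (same section).** The text deals with loss to follow-up. It does not address a STAR that does not exist because there was no episode.

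**The concern.** Severity, hours lost and the episode SF-12 can be observed only after an event that follows randomisation and that tonsillectomy is intended to prevent. If each STAR becomes one record in a random effects model, a participant with no episode contributes nothing. The episodes left in the surgical arm are those that surgery failed to prevent. The two sets of records then differ for reasons other than the effect of treatment on severity, and a random patient intercept does not restore the randomised comparison.

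At stake is the reading of one secondary outcome. If surgery prevents mainly mild episodes, the remaining ones are on average more severe, and the result would appear to count against surgery. If it prevents mild and severe episodes equally, the result is null however large the benefit. In either case the secondary result could seem to conflict with the primary outcome for purely structural reasons.

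**Working it through.** **The plan's own figure.** The article gives no number for this comparison. Its sample size is not in dispute and reproduces: with a difference of 3.6 days, SD 10.8, a two-sided 2.5% type 1 error and 90% power, n = 224 per arm (power 0.901). Then 224 / 0.75 gives 299 per arm, 598 in total, against 600 stated.

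**Step 1: does the text lead to an episode-level comparison?** STARs exist only for episodes; STAR severity is to be compared between arms; repeated secondary measures get a random effects model; the template has one row per patient and occasion. For STAR data the occasions are episodes. No per-participant total, rate or zero is stated. The unit of analysis is thus inferred from these passages together and is not stated outright.

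**Step 2: arithmetic illustration (all inputs assumed).** A control participant has 8 mild episodes (score 1) and 2 severe (score 3). Mean per episode = (8×1 + 2×3)/10 = 1.40; total = 14.

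| Surgery prevents (mild / severe) | Mean per episode | Total | Change in mean | Change in total |
|---|---|---|---|---|
| 75% / 50% | (2×1 + 1×3)/3 = 1.67 | 5 | 19% higher | 64% lower |
| 50% / 50% | (4×1 + 1×3)/5 = 1.40 | 7 | none | 50% lower |
| 50% / 75% | (4×1 + 0.5×3)/4.5 = 1.22 | 5.5 | 13% lower | 61% lower |

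The total falls by half or more in every row, while the per-episode mean moves up, not at all, or down.

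**Step 3: simulation of the model in question (all inputs assumed).** There were 225 participants per arm and 60 runs per scenario. Control episodes were negative binomial with mean 8 over 24 months. Severity had mean 4, between-patient SD 1 and within-patient SD 1.5; below 5 counted as milder. A linear mixed model with a random patient intercept was fitted to episode records only.

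| Prevented (milder / more severe) | Mean total severity, control to surgery | Per-episode estimate, surgery minus control | Runs with surgery significantly worse | No STAR at all, control / surgery |
|---|---|---|---|---|
| 70% / 20% | 32.2 to 16.8 | +0.56 | 98% | 6% / 17% |
| 60% / 40% | 32.2 to 15.6 | +0.20 | 33% | 6% / 15% |
| 50% / 50% | 32.4 to 16.2 | +0.01 | 7% | 6% / 14% |

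Total severity roughly halves in all three scenarios. The model's estimate depends on which episodes were prevented, not on how much burden was removed. The reverse pattern (more severe episodes prevented more often) was not simulated; its direction is shown by the last row of Step 2.

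**The case against.** The strongest reply is that the article never says each STAR becomes a row. The Statistical analysis section does not name STAR, and its random effects sentence fits TOI 14 naturally, because TOI 14 has the same fixed schedule as the SF-12. The article also announces a full statistical analysis plan, which could define per-participant summaries. Some uses of STAR data are clearly aggregate: frequency, counts of visits and prescriptions, and QALYs by area under the curve.

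Much of this stands. The unit of analysis is an inference, and STAR frequency and the counts fall outside the point. What remains is that the article does more than leave the matter open. It frames STAR severity as an arm comparison over episodes experienced and names a model class for repeated secondary measures without exception. An analysis plan that followed this wording would carry the problem forward.

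Two stronger readings are tempting but unsupported. A reader might infer that the trial will show surgery as worse per episode. The article gives no figure on which episodes surgery prevents, and the assumed cases run in both directions. A reader might also infer that participants with many episodes would dominate the comparison. In a random-intercept model with the SDs of Step 3, a participant's relative weight is 1/(1 + 2.25/n): 0.31 for one episode and 0.90 for 20, about 3 to 1 and not 20 to 1.

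Finally, STARs are only requested. Scoring zero for everyone who filed none would mix non-return with benefit, so a simple zero rule is not an adequate repair.

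**Conclusion.** The concern holds in a limited form. As the article is worded, STAR severity and impact (hours lost, and the episode SF-12 if it is compared between arms) would be compared among episodes that occurred. That comparison conditions on a post-randomisation event affected by treatment, and it is not a randomised effect.

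The size cannot be derived from the document. Under the assumed figures, the per-episode contrast runs from 13% lower to 19% higher severity with surgery while total burden falls by 50% to 64%. In the mixed-model simulation it runs from about zero to +0.56 points while total burden roughly halves. These figures show what can happen and do not predict the trial's result.

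The reach is narrow. The primary outcome uses weekly returns sought from all participants. TOI 14 and the scheduled SF-12 are collected at 6, 12, 18 and 24 months whether or not an episode occurs. STAR frequency is a count. None of these is affected, so the wording should be corrected but the main conclusion of the trial is not in danger.

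**What to change.** In Secondary outcomes measures and Statistical analysis:

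1. Define STAR severity and impact as totals per randomised participant over follow-up, for example severity-weighted sore throat days and total hours unable to do usual activities.
2. Compare these totals by randomised arm with follow-up time as exposure, as for the primary outcome.
3. Score zero only for weeks in which the weekly return reports no sore throat days. Treat a week with sore throat days but no STAR, or with no weekly return, as missing. The weekly returns, sought from everyone, make this separation possible.
4. Present severity per episode, and the episode SF-12, descriptively by arm, with a note that these are not randomised comparisons.
5. Report STAR completeness by arm: the share of weeks with reported sore throat days that have a STAR.

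The cost is wording and some derivation work; no new data are needed. There are two downsides. Severity per episode is no longer a tested comparison. The totals also depend on STAR completeness: if returns lapse more in one arm, the missing weeks need explicit handling, because a week with reported sore throat days is known to carry some burden.

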### Economic analysis

‘Within trial’ economic analyses will be carried out from the perspective of the NHS. Costs will be based upon the costs of the randomised interventions received and on the use of subsequent care and services recorded on Case Report Forms and participant-completed questionnaires. Cost falling on participants and their families will also be recorded in a secondary analysis. Participant costs and time away from usual activities per each type of episode of care will be collected via questionnaire at 18 months. A micro costing exercise will be conducted to elicit the other resources required to estimate the costs of the surgical procedures. Other unit costs will come from nationally available data [28] and combined with use of service data to produce a cost for each trial participant. Discounting will be applied to costs and outcomes at UK recommended rates [29].Cost-effectiveness analysis – based on the incremental cost per sore throat day avoided.Cost-utility analysis – based on incremental cost per QALY gained. QALYs will be based upon responses to the SF-12 converted into SF-6D scores using standard algorithms. QALYs will be estimated from the responses from the SF-6D using the AUC method.For both the cost-effectiveness and cost-utility analyses the results will be presented as point estimates of mean incremental costs and effects as well as in stochastic analyses plots of cost and effects and cost-effectiveness acceptability curves.Cost-benefit analysis – a contingent valuation method to allow participants to state their preferences in monetary values [30], to avoid a sore throat day using a participant-completed questionnaire administered at baseline. For each randomised group we will calculate mean willingness to pay and explore how valuations might vary according to participant characteristics (e.g. family income, gender, age, etc.). The data on the willingness to pay for a sore throat day avoided will be combined with information on number of sore throat days experienced and on the cost per participants. The results will be presented as point estimates and in stochastic analysis plots of cost and mean willingness to pay and incremental net benefit curves.

For all economic evaluations deterministic sensitivity analyses will be performed to explore key uncertainties. Where appropriate these analyses will be combined with a stochastic analysis with the results presented in the same ways as described above.

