## Background

The role of tonsillectomy in the management of adult sore throat remains uncertain, and despite demonstrable compliance with prevailing empirical guidance [1], UK regional variation in tonsillectomy rates persists [2]. The 2009 Cochrane review [3] identified only 1 evaluable adult trial with just 70 participants [4] followed up for only 90 days, and the review concluded that reasonable levels of evidence to support clinical decisions were only available for children. Currently there is evidence for increasing numbers of admissions for severe or complicated tonsillitis (e.g. peritonsillar abscess) as the number of tonsillectomy operations has fallen over the past decade in England [5]. The management of sore throats costs the National Health Service (NHS) over £120 million per annum – an estimated £60 million of this for general practitioner (GP) consultations and medical therapy [6]. From 2011–12 in England alone, secondary care costs included an estimated £10 million for bed usage and around £20 million in elective adult tonsillectomy [6].

The questions that patients, doctors and health policy makers wish to answer relate to the relative costs and benefits of tonsillectomy against conservative management (delayed surgery) and whether there can be more refined surgical indications to maximise such benefits, minimise the risks and make the best use of the scarce resources that are available.

Decision-making for tonsillitis is mostly undertaken in primary care where there may be the greatest potential for evolution in the patient pathway. Tonsillectomy is a painful procedure [7], which requires an average of 14 days off work [8, 9] and has a number of less common but intrusive complications [10] including changes in taste and tongue sensation [11, 12]. Thus, irrespective of its relative merits as a treatment, like all surgical intervention it needs to be weighed carefully against the alternatives.

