### Intervention

Participants randomised to the treatment arm will undergo a tonsillectomy within 6–8 weeks of randomisation.

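### Participant time and cost for a tonsillectomy are asked once, at 18 months, about 16 months after planned surgery, so the value used in the secondary patient-perspective analysis appears to rest on long recall

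*Protocol article*

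**What the plan says.** The Economic analysis section fixes when participant burden is measured: "Participant costs and time away from usual activities per each type of episode of care will be collected via questionnaire at 18 months". Table 1 lists the "Participant Time and Travel Questionnaire" with one entry, in the 18-month column.

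The Intervention section says that participants allocated to surgery "will undergo a tonsillectomy within 6–8 weeks of randomisation". The clock for follow-up is set under Data collection and follow-up: "All participants will be followed up for 24 months from the date of randomisation". The Background says that tonsillectomy "requires an average of 14 days off work".

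Sore throat time loss is handled differently. Under Data collection and follow-up, all participants are "requested to submit a STAR when they experience a sore throat", and that return asks for "the number of hours when unable to undertake usual activities (including work/studies"). The same section describes nurse contacts 1 and 2 weeks after tonsillectomy, with adverse events as their stated purpose.

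The secondary objectives and the economic outcome measures name a joint NHS and patient perspective for the cost per sore throat day avoided. The secondary objectives also name NHS and participants for the cost per QALY. The Economic analysis section takes the NHS perspective as its base and places costs to participants and families in a secondary analysis.

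**The concern.** Recovery from the operation is a single block of lost time, concentrated in the surgical arm and, on the protocol's own figure, about two weeks long. It is one of the clearest ways in which participant cost should differ between the arms. On the schedule as written it is recalled more than a year later, while time lost to sore throats is reported close to the event.

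What is at stake is the participant time and cost attached to one tonsillectomy. If people systematically lengthen or shorten their recovery in memory, the error does not cancel. It carries into the incremental participant cost, and so into the patient-perspective ratios that the objectives name.

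**Working it through.** **Inputs from the protocol**
- Questionnaire: 18 months after randomisation, about 78 weeks (Economic analysis; Table 1).
- Planned surgery: 6–8 weeks after randomisation (Intervention).
- Average time off work after tonsillectomy: 14 days (Background).
- Existing booklets: 6, 12, 18 and 24 months (Data collection and follow-up; Table 1).
- Conversion: 365.25 / 12 / 7 = 4.348 weeks per month.

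**Recall gap as scheduled**
- In weeks: 78 − 8 = 70 and 78 − 6 = 72.
- In months: 18 − 8/4.348 = 16.2 and 18 − 6/4.348 = 16.6.
- From the end of a 14-day recovery: 18 − 10/4.348 = 15.7 and 18 − 8/4.348 = 16.2.

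**Recall gap if asked in the 6-month booklet**
- 6 − 8/4.348 = 4.2 and 6 − 6/4.348 = 4.6 months.

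**Is there an earlier record?**
- STAR: triggered by a sore throat and open to both arms. The protocol does not say whether post-operative pain counts, so it may catch some recovery time but is not described as a record of it.
- Nurse calls at 1 and 2 weeks: described for adverse events only.
- Case Report Form at surgery and Health Service Utilisation Questionnaire: both listed in Table 1, but their items are not given.

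So no earlier measurement is described, and none is ruled out.

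**What a recall error would do**

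Collecting values for each type of care episode, and combining unit costs with service use, reads as a unit-value design: one average time and cost per type of episode, multiplied by counts. Let r be the systematic relative error in recalled days, and p_T and p_C the proportions operated on in the tonsillectomy and conservative arms. Then:
- error per operation = 14 × r days;
- error in the between-arm difference = 14 × r × (p_T − p_C) days per participant.

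The protocol gives no value for r. As an assumed range:
- r = 10%: 14 × 0.10 = 1.4 days per operation
- r = 20%: 14 × 0.20 = 2.8 days
- r = 30%: 14 × 0.30 = 4.2 days

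The sign could be either. The between-arm error reaches the per-operation figure only if everyone in the surgical arm and nobody in the conservative arm is operated on; crossover shrinks it.

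**The case against.** The strongest reply is that this is a condensed article. Questionnaire items belong in the full protocol, and the surgery Case Report Form or the utilisation questionnaire may already ask about recovery. STARs also go to both arms, with weekly prompts running through the recovery period. This stands to the extent that the point must be conditional: it holds unless another instrument records recovery time.

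Second, participant costs are secondary in the Economic analysis section, and deterministic sensitivity analyses are planned. That limits the consequence. Sensitivity analyses can show how much the answer moves, but they cannot recover what was never recorded.

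Third, undirected recall error largely averages out over a few hundred operated participants. That is right, and the point concerns systematic error only.

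Fourth, a single late form limits burden and allows most kinds of care episode to occur first. That is a good reason to keep it for GP, walk-in and outpatient episodes. It is a weaker reason for an operation planned in the first two months.

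A reader might go further in three ways that the document does not support:
- **Participants lost before month 18 leave surgery costs missing.** Under a unit-value design, the average from operated responders can be applied to every recorded tonsillectomy, so a missing answer need not mean a missing cost.
- **Control participants operated on after month 18 go uncosted.** The same reasoning applies.
- **The recall error rivals the trial's 3.6-day target difference.** That figure is a difference in sore throat days, the effectiveness outcome. Days off work are a cost input, so the two cannot be compared.

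**Conclusion.** The point holds as a modest one. The participant time and cost value for a tonsillectomy is scheduled to be collected about 16 months after the operation in the surgical arm, and no earlier record is described. Any systematic recall error would apply to every operation costed in the secondary patient-perspective analysis, at 1.4 days per operation for each assumed 10%. Neither its size nor its direction can be taken from the document.

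This rests on three assumptions: surgery takes place at the planned 6–8 weeks, no unlisted item captures recovery time, and the per-episode wording means unit values multiplied by counts. The NHS-perspective result, the QALYs (from SF-12 responses) and the primary outcome do not depend on this questionnaire. This is a cheap improvement to a secondary analysis and does not threaten the trial's main conclusions.

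**What to change.** Ask the surgery items nearer the operation: days away from work and usual activities, travel, out-of-pocket costs and carer time.
- **Surgical arm:** add them to the existing 6-month home booklet, which cuts recall from about 16.2–16.6 to about 4.2–4.6 months.
- **Conservative-arm participants who have a tonsillectomy:** add them to the next scheduled booklet after the operation.
- **18-month form:** keep it for the other types of care episode.

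If another form already collects these items, it is enough to say so and to state which source supplies the tonsillectomy value.

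The cost is a page added to booklets already being sent and a few extra items for operated participants. Recall of more than four months remains in the surgical arm, so the change reduces the problem without removing it. The article gives April 2015 as the planned start of recruitment, so on that timetable the change could be made before any 6-month booklet falls due.

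### Willingness to pay is measured before randomisation but averaged by arm; one pooled value would keep chance valuation differences out of the cost-benefit estimate

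*Protocol article*

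**What the plan says.** The cost-benefit analysis in the Economic analysis section rests on a contingent valuation in which participants state what they would pay "to avoid a sore throat day using a participant-completed questionnaire administered at baseline". Table 1 schedules that questionnaire at baseline and at no other time.

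Data collection and follow-up fixes the order of events: "Once consented, the participant will complete a baseline questionnaire booklet to be returned to NCTU", and next, "The participating site will then randomise the participant via the NCTU randomisation system". The valuation is therefore given before the participant has an allocation.

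Economic analysis then sets the level of averaging: "For each randomised group we will calculate mean willingness to pay". The following sentence says that the WTP data "will be combined with information on number of sore throat days experienced and on the cost per participants". Results are to be shown as point estimates and in "stochastic analysis plots of cost and mean willingness to pay and incremental net benefit curves". The matching objective, under Main trial secondary objectives, refers to the questionnaire "administered at baseline and information on the number of sore throat days experienced" and does not say whether the valuation is common to both arms. No pooled valuation is mentioned anywhere in the article.

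**The concern.** A quantity measured before allocation cannot be changed by allocation. Any gap between the arms in mean WTP is a chance imbalance and says nothing about tonsillectomy. If each arm's sore throat days are multiplied by that arm's own mean, the gap is carried into the difference in monetary benefit. It is scaled by all the days experienced, not only by the days avoided.

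At stake are the precision and the realised point estimate of one of the three planned economic analyses. Resampling WTP in the stochastic analysis would show the extra uncertainty as a wider spread, but it would leave the imbalance in the point estimate.

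**Working it through.** **The plan's own figures.** The article states no number for the cost-benefit analysis, so the Sample size calculation section supplies the scale: a 3.6-day difference, SD 10.8 days, 90% power, type 1 error 2.5%, 224 completers per group, 25% loss, 600 recruited. With a two-sided 2.5%, n = 2 × (2.2414 + 1.2816)² × (10.8/3.6)² = 2 × 12.41 × 9 = 223.4, so 224 per group. Allowing for loss, 224/0.75 = 299 per group, or about 600. The stated figures reproduce.

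**Decomposition.** Let W be an arm's mean WTP per day and D its mean sore throat days, with C for conservative management and T for tonsillectomy. Let W̄ and D̄ be the averages of the two arm means. Then

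W_C·D_C − W_T·D_T = W̄·(D_C − D_T) + D̄·(W_C − W_T).

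The first term is the monetary value of days avoided. The second is baseline imbalance, with expectation zero. Multiplying each participant's own WTP by their own days and averaging by arm carries the same imbalance.

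**Illustration.** With no treatment effect, 20 days in each arm and mean WTP 10% apart, the second term is 20 × 0.10 = 2.0 days' worth of WTP.

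**Size of one standard error.** Dividing by W̄ expresses the term in day-equivalents: SE = D̄ × CV × √(2/n). The coefficient of variation (CV) of WTP and D̄ are assumptions, because the article gives neither. With n = 224, √(2/224) = 0.0945:

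| CV of WTP | D̄ = 10 | D̄ = 20 | D̄ = 30 |
|---|---|---|---|
| 0.5 | 0.47 | 0.94 | 1.42 |
| 1.0 | 0.94 | 1.89 | 2.83 |
| 1.5 | 1.42 | 2.83 | 4.25 |

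Against 3.6 days this runs from 13% (0.47/3.6) to 118% (4.25/3.6). If all 300 per arm supply a baseline WTP, the range is 0.41 to 3.67.

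**What would reverse the sign.** With a realised difference of 3.6 days, the imbalance alone reverses the result when the relative WTP gap exceeds 3.6/D̄: 36%, 18% or 12% at 10, 20 or 30 days. At CV 1 and 20 days that is 3.6/1.89 = 1.9 SE. In the table, only CV 1.5 with 30 days reverses at one SE (4.25 > 3.6).

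**Effect of pooling.** With a single W̄ the second term vanishes. The sampling SE of the days difference is 10.8 × 0.0945 = 1.02. With arm means at 20 days, the SE of the benefit difference is √(1.02² + 0.94²) = 1.39 at CV 0.5, √(1.02² + 1.89²) = 2.15 at CV 1, and √(1.02² + 2.83²) = 3.01 at CV 1.5.

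A simulation of 20,000 trials checked this, with lognormal WTP at CV 1, negative binomial days with means 18.2 and 21.8 and SD 10.8, and 224 per arm. Both methods averaged 3.60 day-equivalents. The SD was 2.16 with arm means and 1.04 with the pooled mean, and the sign was wrong in 4.7% and 0.05% of trials respectively.

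**The case against.** The strongest reply is that the faulty step is inferred. The article does not say that each arm's days are multiplied by that arm's mean. The sentence on group means goes on to how valuations vary with participant characteristics, so it could describe the valuation data only. The combining sentence speaks of the value of an avoided day, which suits a single figure. A journal article may also leave the mechanics to the full plan. The ambiguity is real, and a reader who takes arm-specific pricing as an explicit commitment goes beyond the text. Even so, the article names a level of averaging, by randomised group, and no other. The two sentences are consecutive parts of one analysis, and plots of cost against mean WTP fit arm-specific values. The point concerns that stated choice, not a missing detail.

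A reader might also infer that the analysis is biased. It is not: randomisation makes the expected gap zero, and both methods averaged 3.60 in the simulation. A reader might further infer that a modest imbalance would typically overturn the result. That is not supported either. The size depends on two assumed quantities, and at the low end the term is 13% of the target difference.

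Finally, pooling is not neutral to the estimand. It suits mean WTP times mean days avoided. If the target were the sum of each participant's own valuation of their own avoided days, a single mean would ignore any covariance between valuation and benefit. The Background hypothesises that the more severely affected gain most, so that covariance may not be zero. This stands, and it shapes the fix.

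**Conclusion.** The point holds as one of avoidable imprecision in the cost-benefit analysis. WTP is elicited before randomisation, its mean is to be calculated by arm, and on the natural reading this adds mean days × (W_C − W_T) to the difference in monetary benefit. One SE of that term is 0.47 to 4.25 day-equivalents with 224 per arm, assuming a CV of 0.5 to 1.5 and 10 to 30 mean days. At CV 1 and 20 days, pooling roughly halves the SE of the benefit difference, from 2.15 to 1.02.

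The documents do not support calling this a systematic bias or a likely reversal of the conclusion. The primary outcome, the sample size, the cost per sore throat day avoided and the cost per QALY do not use WTP and are untouched.

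**What to change.** In the Economic analysis section, state that the base-case cost-benefit analysis values sore throat days in both arms with a single WTP estimate pooled over all randomised participants, with its uncertainty carried into the stochastic analysis. Present arm-specific means only as a baseline description, and explore variation by income, gender and age in the pooled sample. If individual valuations are wanted to capture covariance between WTP and benefit, make that a sensitivity analysis adjusted for baseline WTP.

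If the arm means were only ever meant descriptively, the same wording settles it. The cost is about one sentence, or two with the sensitivity analysis, with no new data and no change to the questionnaire schedule.
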